### Sample size

It will be important to detect even modest increments in screening uptake between trial arms, because in a public health program, small effects may yield substantial benefits across the population at risk. We make the statistically conservative assumption that the underlying proportion of people invited who actually receive a Health Check is about 50%. With 4,263 participants in each trial arm, with 12,789 in total, this provides more than 90% power to detect a difference in uptake of Health Checks between each active treatment arm and the standard intervention arm of at least 4%. These calculations are based on 5% significance level by using a Bonferroni correction for three comparisons. The calculations were performed in Stata version 12 [26]. Because present rates of Health Check uptake are below 50% in the study area, slightly greater power may be realized in the study. No planned interim analysis and no stopping guidelines exist, as this trial has a low risk of adverse events.

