## Methods

### Trial design

Three-arm superiority randomized controlled trial with equal allocation to each arm (see Figure 1 for the trial flow diagram).

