### Statistical methods

The analysis will be on an intention-to-treat basis and will include all patients who are randomized, regardless of subsequent actions (for example, if the questionnaire was not sent out, participants will still be analyzed in the group to which they were randomized). For participants who die or leave their general practice within 6 months of the standard invitation, we will use the Health Check uptake status at the end of registration as their outcome.

In an individually randomized trial, Health Check uptake may vary between general practices, as, for example, if a practice nurse follows-up patients for an appointment. We will quantify the extent of between-practice variation by tabulating the outcome by general practice and estimating an intraclass correlation coefficient by using analysis of variance.

To adjust for practice-effect in the primary analysis, we will fit a marginal model by using the method of generalized estimating equations (GEEs), allowing for clustering by practice by using an exchangeable correlation structure and model-based variance estimates, as the number of practices is relatively small [27]. Covariates will be age, gender, month of invitation, deprivation quintile, and arm comparing outcomes between arms A versus B, A versus C, and B versus C, with adjustment for multiple comparisons.

The GEE model will be implemented by using the binomial family and an identity link to estimate the adjusted risk difference. Because we are primarily interested in absolute differences in NHS Health Check uptake, rather than in relative measures such as odds ratios, we will implement covariate adjustment by the method of inverse probability weighting by using the propensity score as suggested by Ukoumunne *et al*. [28]. Interaction terms will be tested, and, where appropriate, intervention effects will be estimated by subgroup. The slope index of inequality (SII) [29] will be used as a metric to estimate the difference in screening uptake between the least- and the most-deprived quintiles (local IMD scores will be classified into quintiles of the distribution of IMD scores in England for reference), and we will test whether SII differs between trial arms.

All estimates will be presented with 95% confidence intervals and *P* values. The trial will be reported according to CONSORT recommendations.

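### Bonferroni, the only multiplicity correction the protocol names, is valid but gives up power: with three arms, Shaffer's step-down controls the same 5% family-wise error and never rejects less

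*Protocol article*

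**What the plan says.** Under Sample size, the protocol article assumes that "the underlying proportion of people invited who actually receive a Health Check is about 50"%. It sets the design as follows: "With 4,263 participants in each trial arm, with 12,789 in total". The claim made for this size is that "this provides more than 90% power to detect a difference in uptake of Health Checks", where the target is 4 percentage points for B v A and for C v A. The error rate is set in one sentence: "These calculations are based on 5% significance level by using a Bonferroni correction for three comparisons". Power is stated only for those two contrasts; no effect size or power is given for B v C.

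Under Statistical methods, the primary model has "arm comparing outcomes between arms A versus B, A versus C, and B versus C, with adjustment for multiple comparisons". The procedure is not named there, and no order or hierarchy is given among the three contrasts. The same section plans 95% confidence intervals and P values for all estimates.

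Under Secondary analyses, the mediation analysis through cognitions is to be run only if uptake differs significantly between the two questionnaire arms. A significance decision on B v C therefore has a direct consequence within the plan.

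**The concern.** Bonferroni treats the three pairwise nulls as if any subset of them could be true. With three arms that is not so. If A = B and A = C, then B = C as well, so exactly two true nulls is impossible: either all three are true, or at most one is. Once one null has been rejected, a correction for the remaining two protects against a configuration that cannot occur.

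The trial has to decide whether each questionnaire arm beats standard invitation and whether the voucher adds anything, and the Sample size section itself stresses detecting modest increments. Under Bonferroni, a contrast with P between 0.0167 and 0.05 that sits beside a clearly significant one is not declared significant. With three arms, control of the 5% family-wise error does not require that.

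**Working it through.** **Inputs from the protocol article.** Uptake 50% v 54%; 4,263 per arm; 5% level divided by three; more than 90% power (all Sample size); equal allocation (Trial design). Two-sided testing is an assumption, because sidedness is not stated. Step 1 supports it.

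**Step 1. Reproduce the stated sample size.** Per-comparison alpha = 0.05/3 = 0.01667, so z = 2.394; for 90% power z = 1.2816. Mean proportion 0.52.

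n = [2.394 × √(2 × 0.52 × 0.48) + 1.2816 × √(0.50 × 0.50 + 0.54 × 0.46)]² / 0.04² = 4,212.6

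With continuity correction: n/4 × [1 + √(1 + 4/(n × 0.04))]² = 4,262.5, which rounds up to **4,263, the stated figure**. An uncorrected alpha of 0.05 would give 3,327 and 0.05/2 would give 3,920, so the trial was sized at two-sided 0.05/3.

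**Step 2. Check the stated power.** Null standard error √(2 × 0.52 × 0.48/4,263) = 0.01082; alternative standard error √(0.4984/4,263) = 0.01081. Power = Φ[(0.04 − 2.394 × 0.01082)/0.01081] = Φ(1.303) = **90.4%**. The claim holds.

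**Step 3. Why the step-down is valid.** Shaffer's rule: reject the smallest P value if it is below 0.05/3; if it is, reject each of the other two that is below 0.05.
- All three nulls true: any false rejection needs the smallest P value to pass 0.05/3, so the error is at most 3 × 0.05/3 = 5%.
- Exactly one null true: it can be rejected only if its own P value is below 0.05, so the error is at most 5%.
- Exactly two nulls true: impossible.

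Any P value below 0.05/3 is rejected by both rules, so Shaffer never rejects less than Bonferroni.

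**Step 4. Size of the loss.** Simulation of 400,000 trials per scenario, 4,263 per arm, pooled two-proportion z tests. The uptakes are assumptions, except that 50% and a 4-point effect are the design values. Practice clustering and covariate adjustment are ignored.

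| Assumed uptake A/B/C | Quantity | Bonferroni | Shaffer |
|---|---|---|---|
| 50/54/54% | both active arms superior to A | 83.9% | 91.9% |
| 50/54/54% | A v B (A v C alike) | 90.4% | 94.4% |
| 50/54/56% | A v B | 90.3% | 95.9% |
| 50/54/56% | B v C | 29.7% | 45.8% |
| 50/54/57% | B v C | 65.5% | 79.8% |
| 50/54/58% | A v B | 90.4% | 95.9% |
| 50/54/58% | B v C | 90.9% | 96.1% |
| 50/53/55% | A v B | 64.7% | 79.0% |
| 50/52/54% | A v B | 29.3% | 44.9% |
| 50/52/54% | B v C | 29.1% | 44.6% |
| 35/39/41% | B v C | 30.6% | 47.3% |

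The last row uses 35%, the midpoint of the local rates of 32% and 38% under Setting and participants.

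**Step 5. Error rate in simulation.** With all arms equal at 50%, family-wise error is 4.4% under either rule. With exactly one pair equal it is 4.9% to 5.1% under Shaffer, which is 5% within simulation error, and 1.6% to 1.7% under Bonferroni.

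**The case against.** The strongest objection is that the Bonferroni sentence describes how the trial was sized, not how P values will be adjusted. A reader might infer that the protocol fixes single-step Bonferroni for the analysis. It does not: Statistical methods only promises an adjustment, and sizing on Bonferroni while analysing with a step-down method would fit the text. A statistical analysis plan that is not shown may name a method. This stands, and it makes the point conditional. It does not remove it, because Bonferroni is the only correction named and therefore the natural one to carry forward.

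Second, a reader might infer an error in the design. There is none: Bonferroni controls the family-wise error, 4,263 per arm reproduces exactly, and the stated power is met.

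Third, a reader might infer that voucher v no voucher loses most. The protocol gives no B v C effect, so this cannot be said in general. It is true in the 50/54/56% and 50/54/57% scenarios. At 50/52/54% A v B and B v C lose about the same (about 16 points each), and at 50/54/58% both lose about 5. If the voucher adds nothing, there is no B v C power to gain.

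Fourth, Bonferroni has directly matching simultaneous intervals (each at 1 − 0.05/3 = 98.3%) and step-down testing does not. In a trial mainly interested in absolute differences this is a real trade-off. It weighs less here because the protocol plans 95% intervals and does not describe them as simultaneous.

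**Conclusion.** The point holds as a low-cost gain in efficiency, not as a correction of a mistake. If Bonferroni is used in the analysis, it gives up power that the 5% family-wise error does not require. At the design effect in both active arms (50/54/54%), the loss is about 8 points for showing both superior (83.9% v 91.9%) and about 4 points per arm. For a B v C difference of 2 to 3 points with B 4 points above A, it is about 14 to 16 points. The largest contrast gains little: A v C at 50/52/54% goes from 90.4% to 91.1%.

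That Shaffer's rule is valid and never rejects less follows from the logic of three pairwise nulls and rests on no scenario. The power figures rest on the assumed uptakes, two-sided tests and no allowance for clustering or covariates.

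**What to change.** Under Statistical methods, before outcome data are seen, replace the general reference to an adjustment with wording such as: *The three pairwise comparisons will be tested by Shaffer's step-down procedure at a two-sided family-wise level of 5%: the smallest P value at 0.05/3 and, if significant, the other two each at 0.05. Adjusted P values will be reported.* The adjusted values are 3 × p(1) for the smallest (capped at 1), and for each of the others the larger of its own P value and that figure.

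Keep the Bonferroni statement under Sample size as the conservative design basis. The claim of more than 90% power remains true.

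The cost is one sentence in the protocol or analysis plan, with no additional participants or data. The downside is that step-down decisions have no simple matching simultaneous intervals. Show the planned 95% intervals beside the adjusted P values, and say that the intervals are not adjusted for multiplicity.

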### Blinding

Participants’ GPs have provided consent to their participation in the trial, and so participants are not overtly aware that other trial arms exist. However, participants in Groups B and C receive a postal intervention and thus cannot be blind to their group allocation. The study team is blind to participants’ details during group allocation and blind to group allocation during extraction of participant data and outcome from GP records.

### Statistical methods

The analysis will be on an intention-to-treat basis and will include all patients who are randomized, regardless of subsequent actions (for example, if the questionnaire was not sent out, participants will still be analyzed in the group to which they were randomized). For participants who die or leave their general practice within 6 months of the standard invitation, we will use the Health Check uptake status at the end of registration as their outcome.

In an individually randomized trial, Health Check uptake may vary between general practices, as, for example, if a practice nurse follows-up patients for an appointment. We will quantify the extent of between-practice variation by tabulating the outcome by general practice and estimating an intraclass correlation coefficient by using analysis of variance.

To adjust for practice-effect in the primary analysis, we will fit a marginal model by using the method of generalized estimating equations (GEEs), allowing for clustering by practice by using an exchangeable correlation structure and model-based variance estimates, as the number of practices is relatively small [27]. Covariates will be age, gender, month of invitation, deprivation quintile, and arm comparing outcomes between arms A versus B, A versus C, and B versus C, with adjustment for multiple comparisons.

The GEE model will be implemented by using the binomial family and an identity link to estimate the adjusted risk difference. Because we are primarily interested in absolute differences in NHS Health Check uptake, rather than in relative measures such as odds ratios, we will implement covariate adjustment by the method of inverse probability weighting by using the propensity score as suggested by Ukoumunne *et al*. [28]. Interaction terms will be tested, and, where appropriate, intervention effects will be estimated by subgroup. The slope index of inequality (SII) [29] will be used as a metric to estimate the difference in screening uptake between the least- and the most-deprived quintiles (local IMD scores will be classified into quintiles of the distribution of IMD scores in England for reference), and we will test whether SII differs between trial arms.

All estimates will be presented with 95% confidence intervals and *P* values. The trial will be reported according to CONSORT recommendations.

### Secondary analyses

To understand the processes of responding to the intervention, analyses will be implemented to determine whether completing the QBE questionnaire, as opposed to receiving but not completing the questionnaire, is necessary to obtain the observed effects. We will compare the proportions of patients who attend Health Checks among participants who received and completed the questionnaire for the QBE arm (completers) and the QBE + incentive arm (incentive-completers), as well as participants in the QBE arm who received but did not complete the questionnaire (noncompleters) and participants in the QBE + incentive arm who received but did not complete the questionnaire (incentive-noncompleters), and those who did not receive the questionnaire.

We will also examine whether having higher or more-positive cognitions (that is, attitude, subjective norms, perceived behavioral control, anticipated regret, intentions) about the Health Check, when completing the QBE questionnaire is associated with increased rates of attendance. Therefore, we will compare the proportions of patients who attend Health Checks for positive completers (those with high scores on the cognitions) and negative completers (those with low scores on the cognitions). If significant differences in uptake appear between the QBE and QBE + incentive arms, we will examine whether these are mediated by differences in cognitions [30].

The response rate to the QBE questionnaire will be analyzed both overall, for each treatment group, and by deprivation quintile. The distributions of responses to questionnaire items will be evaluated by deprivation quintile. We plan to access the results of the participants’ Health Checks, in terms of level of cardiovascular risk, and compare these by trial arm. We will compare Health Check results for questionnaire responders and nonresponders. These analyses will thus describe the pattern of response to the intervention in terms of both deprivation category and level of cardiovascular risk.

Secondary analyses to examine whether outcomes and intervention effects vary by deprivation quintile, gender, or age-group will be performed in a similar manner as stated earlier and will include exploring interaction effects. The delay in uptake between arms will be examined by using time-to-event analysis. The duration between the date the invitation was sent and the booked appointment will be calculated. Differences will initially be visually assessed by using Kaplan-Meier curves, and then an appropriate time-to-event model with robust variance estimates allowing clustering by practice will be fitted, adjusting for age, gender, month, and deprivation quintile.

To evaluate the consistency of estimates obtained by using the two different randomization methods, subgroup analyses will be performed for each randomization method separately. A meta-analysis will be performed, by using each participating general practice as the unit of analysis, with results pooled for each randomization method separately and across all practices. A test for heterogeneity will be performed.

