### Financial incentives to increase response rates to questionnaires

Strong evidence suggests that financial incentives for questionnaire return increase response rates. A systematic review, including 94 trials with a pooled total of 160,004 participants, found that the odds of returning a postal questionnaire were almost doubled if a financial incentive was offered [20]. As the Question-Behaviour Effect is greater among individuals who return a questionnaire [17], incentivizing questionnaire return may increase the size of any effect of a questionnaire on uptake of the NHS Health Check. A meta-analysis of 85,671 participants in 88 randomized trials of financial incentives to increase response rates for mailed questionnaires reported a significant increase in response rates for incentives up to the value of $5 [21].

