### What is the potential impact on socioeconomic inequalities in uptake?

Death rates from coronary heart disease are highest in areas of greatest deprivation [1], so considering socioeconomic inequalities in the evaluation of any intervention to increase uptake of NHS Health Checks is important. Although evidence suggests that enhanced invitation methods, such as a QBE-based questionnaire, increase uptake of screening and performance of health-related behaviors, we do not know their impact on the NHS Health Checks, a relatively new program. The impact of the QBE on inequalities in uptake is also unknown. Individuals experiencing greater levels of deprivation may find it more difficult to convert their positive attitudes toward Health Checks, and their intentions to attend, into action. One of the possible mechanisms of action of the QBE is that it makes individuals’ attitudes more cognitively accessible and thus may increase the likelihood that individuals from deprived backgrounds attend. Alternatively, although we do not know if level of deprivation influences attitudes toward NHS Health Checks, evidence from cancer screening suggests that individuals experiencing greater levels of deprivation perceive fewer benefits and greater barriers to attending [22].

The QBE is stronger for individuals with positive attitudes toward, and intentions for, the behavior [17]; therefore the QBE may enhance inequalities in uptake, if any do exist. The offer of a financial incentive may increase questionnaire return rates only among those with already positive attitudes toward NHS Health Checks, so should result in increased uptake. However, if the offer of a financial incentive increases questionnaire return rates among those with less-positive attitudes, it is likely to have a lesser impact on uptake.

Little research examines how and if incentives influence uptake of screening differentially across deprivation [23]. The offer of a financial incentive may be most attractive for individuals who are experiencing deprivation and so may increase the strength of the QBE on Health Check uptake, particularly in individuals from deprived backgrounds. It will be important to consider inequalities in uptake in any investigation of the impact of the QBE on uptake of NHS Health Checks.

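### Whether completing the questionnaire is necessary for the effect is to be judged by comparing self-selected completers with non-completers, a contrast that selection alone can produce

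*Protocol article*

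**What the plan says.** The Secondary analyses section of the Protocol article states a causal aim: to determine "whether completing the QBE questionnaire, as opposed to receiving but not completing the questionnaire, is necessary to obtain the observed effects". The method follows in the next sentence: "We will compare the proportions of patients who attend Health Checks among participants who received and completed the questionnaire for the QBE arm", with the same for the incentive arm, for recipients in each arm who did not complete it, and for people who did not receive it. For this comparison the section gives no adjustment, no contrast that keeps the randomization, and no warning that the result is an association. The next paragraph, on cognitions, does speak of association.

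The Background bears on this in three places:
- On incentives, it reasons from a premise of the same kind: "As the Question-Behaviour Effect is greater among individuals who return a questionnaire". It also reports from a systematic review that "the odds of returning a postal questionnaire were almost doubled if a financial incentive was offered".
- On inequalities, it considers that the voucher "may increase questionnaire return rates only among those with already positive attitudes toward NHS Health Checks". It also allows that the voucher may draw returns from people with less positive attitudes.
- In the same section it states that "The QBE is stronger for individuals with positive attitudes toward, and intentions for, the behavior".

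**The concern.** Whether completion is necessary is a question about what would happen to the same people with and without completing. The planned groups do not contain the same kind of people. Completers and non-completers are two self-selected parts of a randomized arm, while arm A is a whole randomized arm. If motivation drives both return and attendance, splitting arm B by return moves one part above A and the other below A with no effect of the questionnaire at all. That is the pattern a reader would take as showing that completion is needed. The same selection can mask a real benefit of receiving the questionnaire without returning it.

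At stake is the explanation of how the intervention works, not the primary result. The Background already moves from a larger effect in returners to the case for rewarding return, and this table could appear to confirm that mechanism whether or not it is true.

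**Working it through.** **1. The plan's own figure.** Inputs from Sample size: 50% versus 54%, 5% significance with Bonferroni correction for three comparisons (0.05/3 = 0.0167, taken as two-sided), 90% power. The normal-approximation formula gives 4,213 per arm, and 4,263 with continuity correction, which matches the stated 4,263. The yardstick is therefore a 4-point difference with 4,263 per arm.

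**2. False gap when the questionnaire has no effect.** Let U be overall uptake, R the return rate, u_c and u_n uptake in completers and non-completers. Solve

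- R × u_c + (1 − R) × u_n = U
- [u_c/(1 − u_c)] / [u_n/(1 − u_n)] = OR

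U spans the local 32% and 38% (Setting and participants) up to the 50% of Sample size. R = 10-40% and OR = 1.5-3 are assumptions, since the article gives neither.

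For U = 35%, R = 30%, 4,263 in the arm:

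| OR | Completers | Non-completers | Gap (points) | z |
|---|---|---|---|---|
| 1 | 35.0% | 35.0% | 0 | 0 |
| 1.5 | 41.6% | 32.2% | 9.4 | 5.8 |
| 2 | 46.3% | 30.1% | 16.2 | 9.9 |
| 3 | 53.0% | 27.3% | 25.7 | 15.9 |

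Check at OR 2: 0.30 × 0.463 + 0.70 × 0.301 = 0.350.

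Over U = 32-50%, R = 10-40% and OR = 1.5-3 the gap is about 9 to 27 points. Taking arm A as the group that did not receive the questionnaire does not repair this: completers lie about 5 to 24 points above A, and non-completers about 1 to 11 points below.

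**3. A second null model.** One latent motivation score drives both return and attendance; 1,000 simulated trials per scenario, 4,263 per arm, U = 35%, R = 20-30%, tests at 0.05.

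| OR per SD of motivation | Gap (points) | Completer vs non-completer significant | Randomized B vs A significant |
|---|---|---|---|
| 1.65 | about 5 | 82-91% | about 5% |
| 2.72 | about 17 | 100% | about 4-6% |

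The randomized contrast keeps its error rate; the completer contrast does not.

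**4. Masking.** At U = 35%, R = 30%, OR = 2, non-completers start at 30.1%, which is 4.9 points below A. A true 4-point benefit in them would show as 30.1 + 4 − 35.0 = −0.9 points.

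**5. What the randomized voucher can offer.** The instrumental estimate is (uptake C − uptake B)/(return C − return B), with expected value 0 when the questionnaire does nothing. At 35% uptake the standard error of the numerator is √(2 × 0.35 × 0.65/4263) = 0.0103, so its 95% half-width is 1.96 × 0.0103 ≈ 0.020. Divide by the shift in return if the voucher doubles the odds of return (starting rates assumed; sampling error in the denominator ignored):

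| Return in B | Return in C | Shift (points) | 95% half-width (points) |
|---|---|---|---|
| 10% | 18% | 8.2 | about 25 |
| 20% | 33% | 13.3 | about 15 |
| 30% | 46% | 16.2 | about 13 |
| 40% | 57% | 17.1 | about 12 |

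**The case against.** The analysis is secondary and is framed as understanding how people respond. The section states no decision rule, keeps the two questionnaire arms apart, reports response rates by group, and plans mediation analysis if B and C differ. The authors plainly know that return may depend on attitude. A full analysis plan may add adjustment and caveats. The proposed alternative is imprecise.

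Much of this limits the consequence, but it does not remove the mismatch. The aim and the method are both stated, and the method cannot answer the aim. Adjustment would help only in part: the cognitions are measured by the questionnaire itself, so they are unknown in non-completers. Keeping the voucher arms apart does not help within each arm, and comparing completers across arms is also selected, because the voucher changes who completes.

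A reader might go further in two ways that the article does not support.
- **That the false effect must be very large.** If returners would attend at 60% anyway, with 35% uptake and 30% return, non-completers attend at (0.35 − 0.30 × 0.60)/0.70 = 24.3%, a gap of 36 points. But this implies an odds ratio of about 4.7, which nothing in the article fixes. The same formula gives 25 to 42 points over 20-40% return and 55-60% returner uptake, and with no association there is no gap. Nor is a conclusion that completion is needed certain, since no rule for reading the table is stated.
- **That the table would wrongly justify paying for returns in a roll-out.** Statistical methods prespecifies B versus C by intention to treat, and that is the test of whether the voucher raises uptake. Economic evaluation depends on an enhanced arm beating standard practice. No passage ties the completer table to a payment decision.

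**Conclusion.** The concern holds in a bounded form. A comparison of groups formed by participants' own return is set to answer a causal question, and under no effect it yields a gap whenever motivation drives both return and attendance. The direction rests on that link, which the article raises as a possibility. The size, about 9 to 27 points (about 5 under the weak motivation model), rests on assumed return rates and associations. Even the weak scenario exceeds the 4-point target difference. The primary analysis, the sample size and the three randomized contrasts stand. The change is worth making before analysis, but nothing in the main result depends on it.

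**What to change.** 1. Reword the aim, and report the completer/non-completer table as association only, not as evidence that completion is necessary.
2. For the causal question, use the randomized voucher as an instrument: (uptake C − uptake B)/(return C − return B), with a confidence interval. Interpret it as the effect of completing among people whose return is changed by the voucher. State that this requires the voucher to affect uptake only through return, and to deter nobody from returning.
3. Present the derived effect of receipt without return, (uptake B − uptake A) − return in B × that ratio, only as a sensitivity analysis, if at all. It assumes a constant effect of completing, which the Background questions by expecting a stronger effect in people with positive attitudes.

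The cost is a small amount of extra analysis on data already collected. The downside is imprecision: a half-width of about 12 to 25 points means that the trial may be unable to settle the question, and the report should say so.
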